## Abstract

**Background:**

Morocco is facing a growing prevalence of diabetes and according to latest figures of the World Health Organization, already 12.4% of the population are affected. A similar prevalence has been reported for gestational diabetes (GDM) and although it is not yet high on the national agenda, immediate and long-term complications threaten the health of mothers and future generations. A situational analysis on GDM conducted in 2015 revealed difficulties in access to screening and delays in receiving appropriate care. This implementation study has as objective to evaluate a decentralized GDM detection and management approach through the primary level of care and assess its potential for scaling up.

**Methods:**

We will conduct a hybrid effectiveness-implementation research using a cluster randomized controlled trial design in two districts of Morocco. Using the health center as unit of randomization we randomly selected 20 health centers with 10 serving as intervention and 10 as control facilities. In the intervention arm, providers will screen pregnant women attending antenatal care for GDM by capillary glucose testing during antenatal care. Women tested positive will receive nutritional counselling and will be followed up through the health center. In the control facilities, screening and initial management of GDM will follow standard practice. Primary outcome will be birthweight with weight gain during pregnancy, average glucose levels and pregnancy outcomes including mode of delivery, presence or absence of obstetric or newborn complications and the prevalence of GDM at health center level as secondary outcomes. Furthermore we will assess the quality of life /care experienced by the women in both arms. Qualitative methods will be applied to evaluate the feasibility of the intervention at primary level and its adoption by the health care providers.

**Discussion:**

In Morocco, gestational diabetes screening and its initial management is fragmented and coupled with difficulties in access and treatment delays. Implementation of a strategy that enables detection, management and follow-up of affected women at primary health care level is expected to positively impact on access to care and medical outcomes.

**Trial registration:**

The trial has been registered on clininicaltrials.gov; identifier NCT02979756; retrospectively registered 22 November 2016.

## Plain English summary

A situational analysis on gestational diabetes in Morocco revealed that pregnant women are experiencing difficulties in accessing GDM screening coupled with delays in receiving appropriate care for those affected. To evaluate a decentralized GDM detection and management approach through the primary health care level in Morocco, we are conducting a hybrid effectiveness-implementation research using a cluster randomized controlled trial design in two districts. In each district, 10 health centers were randomly selected with half of them serving as intervention and half as control facilities. In the intervention arm, women attending antenatal care will be screened for GDM and women positively tested will receive nutritional counselling and follow up through their health centers. In the control facilities, screening and initial management of GDM will apply standard practice. Birthweight of newborns of women with GDM will be compared between both groups and the prevalence of GDM at health center level assessed. We will further explore the quality of life and the care experienced by the women in both arms through a structured survey. In focus group discussions with providers we will explore and evaluate the feasibility of the intervention at primary level and its adoption by the health care professionals.

The findings of this study will be used to inform national stakeholders and are expected to contribute to an adaptation of the current strategy of detection and management of GDM in Morocco.

## Background

In Morocco, a country with a total population of 33.8 million, an estimated 1.67 million people suffer from diabetes [1]. With a current prevalence of diabetes in Morocco of 7.7%, this number is expected to double in the next 20 years. [1] Women of childbearing age are not exempted from this development and alone in the MENA region, 3.7 million babies are born to mothers affected by gestational or pre-existing diabetes [1]. The prevalence of gestational diabetes (GDM) in Morocco is estimated to range between 8.2 and 10% [2, 3]. These figures originate from prevalence studies conducted at two university hospitals, but prevalence rates at lower levels of care are yet unknown. While Morocco has made considerable progress in lowering maternal mortality in the past decades [4], there is now an increased focus on maternal morbidity, including the effects of non-communicable diseases such as gestational diabetes on maternal and neonatal health [5].

Recommendations of high risk pregnancy management including the detection of GDM are available in Morocco and a fasting blood glucose test is routinely recommended to screen for diabetes during antenatal care (ANC). However, a situation analysis indicated that GDM screening is facing various obstacles particularly at the primary level of care. [6] These include gaps in provider knowledge, delays related to blood testing or to specialist referral. Oral glucose tolerance tests are not routinely prescribed unless on specific request. These delays in the detection and treatment of GDM impinge a timely management of affected women who as a result may end up with complications that could have been prevented. The detection and initial management of GDM during ANC through the first level of care could be an appropriate approach to establish timely interventions. However, it is uncertain if such a strategy would be feasible in the context of the Moroccan public health sector. To close this knowledge gap, the study presented in this protocol aims at implementing and evaluating GDM screening and follow up through first line health care services in Morocco.

## Methods/design

### Design

We opted for a hybrid effectiveness-implementation research using a cluster randomized controlled trial design. This design allows to evaluate both clinical effectiveness of the proposed strategy and its implementation at the first level of care guided by its potential for national scaling up [7].

### Study setting

The proposed study will take place in the region of Marrakech-Safi, a region with poor maternal health indicators and one of the priority regions of the Moroccan Ministry of Health. The two study districts Marrakech and Al Haouz, where we already conducted a situational analysis on GDM in 2015 [6], have been selected for the strategy implementation. Marrakech is essentially urban whereas Al Haouz is a rural mountainous district with difficult geographical access to services. Together, the districts have a total population of 1.9 million with 92 public health centres and 53 dispensaries providing primary health care services [8].

### Unit of randomization

The unit of randomization will be the health center (cluster). Cluster randomization rather than individual randomization will be applied to limit contamination between the different arms. In each of the two districts we will randomly select 10 health centers with at least 30 or more antenatal care consultations a month. Of these 10 health centers in each district, 5 are being randomized into the intervention group and 5 health centers serve as controls. As simple random selection does not account for contiguity, adjustments for “inter-cluster” effects will be done in the analysis stage.

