### Population and sample size

All pregnant women attending ANC will be eligible to participate in the study. Pregnant women with a known diabetes type 1 or 2 will be excluded from participation. In each health center, at least eight women diagnosed with gestational diabetes will be identified and followed up during their pregnancies and up to eight weeks post-partum. The sample size of minimum eight women per cluster was calculated based on the assumption that neonatal birth weight will differ in both groups with lower birthweights in the intervention arm due to earlier screening and treatment initiation at health center level. Based on comparisons of birthweight in treated versus untreated mothers [9, 10], for the assumption of a weight difference of 300 g between intervention and control group, a power of 80%, an alpha of 0.05 and an intra-class correlation coefficient of 0.1, we require 75 women with GDM in each arm.

A subsample of four women per district and arm will be selected for in-depth interviews based on the their educational level (≤primary / ≥secondary); and distance from the health center (<30 min / >1 h). Furthermore, the health care providers from both intervention and control facilities who are involved in GDM detection and management will be requested to participate in a focus group discussion (2 FGDs per district).

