### Data analysis

Quantitative data will be double entered into a pre-formatted excel file by the research assistants and converted into STATA Version 13 for further statistical analysis. The analysis will be applied on all recruited women following the intention-to-treat principle. Comparison of categorical variables will be done by using the chi-square/ Fisher’s exact test while continuous variables will be analyzed by using the Wilcoxon rank-sum test. Regression analysis will be applied to assess the relationship between the primary outcome birthweight and maternal determinants.

Qualitative data collection includes interviews with key informants, a sample of pregnant mothers and focus group discussions with providers. The recordings will be translated (those conducted in Arabic or Berber) and transcribed verbatim, followed by a thematic content analysis. Two independent researchers will code the data using NVIVO Version 11. Codes will then be grouped into categories and findings charted into a framework matrix.

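### Health centres are randomised within two contrasting districts, but no analysis named in the article includes district; if birthweight differs between districts, a cluster-adjusted analysis without it is conservative and less precise

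*Protocol article*

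**What the plan says.** The abstract gives 20 clusters in a 1:1 ratio: "we randomly selected 20 health centers with 10 serving as intervention and 10 as control facilities". The Unit of randomization section shows that the allocation was made within district: "Of these 10 health centers in each district, 5 are being randomized into the intervention group and 5 health centers serve as controls". The Study setting section describes the two strata as very different: "Marrakech is essentially urban whereas Al Haouz is a rural mountainous district with difficult geographical access to services".

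The analysis text is short. Under Data analysis, categorical variables get chi-square or Fisher's exact tests, and "continuous variables will be analyzed by using the Wilcoxon rank-sum test". A regression will relate birthweight to characteristics of the mother. Under Outcome variables, the comparison of birthweight between arms is to be adjusted for gestational age, and no other covariate is named. The Unit of randomization section also promises an adjustment for inter-cluster effects at the analysis stage. It gives as the reason that simple random selection takes no account of neighbouring centres. It does not define the adjustment or mention district.

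**The concern.** When allocation is stratified, the arms are balanced on the stratum by design. A difference in mean birthweight between the districts then adds nothing to the true sampling error of the arm difference. An analysis without the stratum still counts that difference in its error term. The estimated standard error is too large, the interval too wide, and a test that is otherwise correct rejects less often than its nominal 5%.

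At stake is power in a trial with little to spare: 20 clusters, a target of 80%, and a cluster-level test that has about 78 to 79% on the article's own inputs once the few degrees of freedom are counted.

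**Working it through.** **Inputs from the Population and sample size section.** Effect: "a weight difference of 300 g between intervention and control group". Further: "a power of 80%, an alpha of 0.05 and an intra-class correlation coefficient of 0.1". Cluster size: "In each health center, at least eight women diagnosed with gestational diabetes will be identified". Stated result: "we require 75 women with GDM in each arm".

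**Assumptions.** The article gives neither the SD nor the sidedness of alpha. I take SD 500 g and a two-sided test. The difference D in mean birthweight between districts is not given and is varied.

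**Step 1: reproduce the sample size.**
- Unclustered n per arm = 2 × [500 × (1.960 + 0.842) / 300]² = 43.6, so 44.
- Design effect = 1 + (8 − 1) × 0.1 = 1.7.
- 44 × 1.7 = 74.8, so 75 per arm, as stated. An SD of about 493 to 509 g gives 75 within tolerance, so 500 g is a reasonable working value. Ten centres of eight give 80 per arm.

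**Step 2: variance of a centre mean.**
- Between centres: 0.1 × 500² = 25,000.
- Within centres: 0.9 × 500² / 8 = 28,125.
- Total 53,125, of which 25,000 / 53,125 = 47% is between centres.
- True SE of the arm difference with ten centres per arm: √(2 × 53,125 / 10) = 103.1 g.

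**Step 3: what leaving district out does.** With five centres per district in each arm, a gap D raises the expected within-arm sample variance of centre means by (10/9) × D²/4. With D added on top of the ICC:
- D = 100 g: 53,125 + 2,778 = 55,903, estimated SE √(2 × 55,903 / 10) = 105.7 g.
- D = 200 g: 53,125 + 11,111 = 64,236, estimated SE √(2 × 64,236 / 10) = 113.3 g.

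The true SE stays at 103.1 g in both cases. Degrees of freedom are 20 − 2 = 18 without district and 20 − 3 = 17 with it. The t multipliers are 2.101 and 2.110, so the price of the term at D = 0 is about 0.4% in interval width.

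**Step 4: simulation.** There were 20,000 trials per setting, analysed by a t-test on centre means without district and by the same model with district. D is either added on top of the ICC of 0.1 or taken to be part of it, in which case D²/4 comes out of the 25,000. Each cell shows without → with district.

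| D | Reading | Type I error | Power for 300 g | Mean 95% CI half-width |
|---|---|---|---|---|
| 0 g | added (no gap) | 0.051 → 0.051 | 78.5% → 78.4% | 213 → 214 g |
| 100 g | added | 0.044 → 0.049 | 77.2% → 78.5% | 219 → 214 g |
| 100 g | within ICC | 0.043 → 0.048 | 78.7% → 79.9% | 214 → 209 g |
| 200 g | added | 0.035 → 0.052 | 72.2% → 78.2% | 235 → 215 g |
| 200 g | within ICC | 0.031 → 0.051 | 80.1% → 86.0% | 216 → 193 g |
| 300 g | added | 0.019 → 0.052 | 64.6% → 78.4% | 259 → 214 g |

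The interval widths agree with step 3. At 200 g, 235 / 215 = 1.09, against (2.101 × 113.3) / (2.110 × 103.1) = 1.09.

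**Step 5: the test the article names.** In the same simulations the individual-level rank-sum test had a type I error of about 0.11 to 0.13 for D from 0 to 300 g added to the ICC. It is 0.13 at D = 0, so clustering, and not the missing stratum, causes it.

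**The case against.** The article is silent on district; it does not exclude it. Its analysis section is a short outline, and a statistical analysis plan may exist. The comparison adjusted for gestational age needs a model whose full covariate list is not given, so the rank-sum test cannot be the whole primary analysis. The inter-cluster sentence confirms that more is planned. All of this stands, and it would be wrong to read the article as having decided to pool the districts. What remains is that the article names its tests and one adjustment, and that these do not match its own allocation. Its only other promised adjustment is tied to neighbouring centres.

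The size is also open to challenge. The article contrasts the districts on setting and access, not on birthweight. A 200 g gap inside the ICC would use 10,000 / 25,000 = 40% of all between-centre variance, which is a lot; 100 g uses 10%. In that reading, power without district stays near the planned 80%, and the term adds power above plan. A shortfall against plan appears only if the gap comes on top of the ICC.

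A reader might also infer three stronger things:
- **Variation between centres dominates the standard error.** It does not; on these inputs it is 47% of the variance of a centre mean.
- **Leaving district out risks false positives.** The effect runs the other way: the cluster-level test falls below 5%.
- **The conservative figures describe the planned test.** They describe a cluster-level t-test, which the article does not name. The rank-sum test that it does name, applied to individual women, is anticonservative because it ignores clustering.

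**Conclusion.** The point holds as a low-cost improvement to the stated analysis. It is not an error that invalidates the trial. Allocation is stratified by district, and no named analysis uses the stratum.

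The consequence is conditional on a birthweight gap that the documents do not supply: nil at 0 g, small up to about 100 g, and material from about 150 to 200 g. The direction does not depend on whether the gap is added to the ICC or lies within it; the table gives the size under each reading. The figures rest on SD 500 g, a two-sided alpha of 0.05, ICC 0.1, exactly eight women in each of 20 centres, and a cluster-level analysis. Only birthweight was examined, so nothing here shows a gain for the complication outcomes.

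**What to change.** State in the Data analysis section, or confirm in the statistical analysis plan, that the primary birthweight comparison uses a cluster-adjusted model with arm, district (fixed effect) and gestational age. An analysis of centre means should likewise carry a district term. For secondary comparisons, use district as a stratum where event numbers allow; rare complications with about 75 women per arm may not support it.

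The cost is one line of text and one degree of freedom, with about 0.1 point of simulated power lost if the districts do not differ (78.5% against 78.4%). The district term must sit inside a model that accounts for clustering. Added to an individual-level test that does not, it would leave the inflated type I error of that test in place, and that problem needs its own correction.

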### Population and sample size

All pregnant women attending ANC will be eligible to participate in the study. Pregnant women with a known diabetes type 1 or 2 will be excluded from participation. In each health center, at least eight women diagnosed with gestational diabetes will be identified and followed up during their pregnancies and up to eight weeks post-partum. The sample size of minimum eight women per cluster was calculated based on the assumption that neonatal birth weight will differ in both groups with lower birthweights in the intervention arm due to earlier screening and treatment initiation at health center level. Based on comparisons of birthweight in treated versus untreated mothers [9, 10], for the assumption of a weight difference of 300 g between intervention and control group, a power of 80%, an alpha of 0.05 and an intra-class correlation coefficient of 0.1, we require 75 women with GDM in each arm.

A subsample of four women per district and arm will be selected for in-depth interviews based on the their educational level (≤primary / ≥secondary); and distance from the health center (<30 min / >1 h). Furthermore, the health care providers from both intervention and control facilities who are involved in GDM detection and management will be requested to participate in a focus group discussion (2 FGDs per district).

### Intervention

In the intervention facilities, all women attending ANC will be offered a fasting glucose test at their first ANC visit and a 75 g oral glucose tolerance test (OGTT) if they are between 24 and 28 weeks pregnant. Tests will be done directly at the health center by capillary glucose testing using a standard plasma-calibrated glucometer. This corresponds to the latest consensus recommendations of FIGO for settings where no laboratories are available [11].

Women who are being diagnosed with gestational diabetes in the intervention facilities will receive nutritional counselling to start first a nutritional therapy combined with regular exercise for the duration of two weeks [12]. Standardization of nutritional counselling will be supported by an initial training of intervention site providers on nutritional education and accompanied by a nutritional guideline and a patient brochure for GDM in French and Arabic developed by the Moroccan Ministry of Health. In case dietary measures will not be sufficient to control glucose values within two weeks, women will be referred to an endocrinologist for further management. Follow-up will be assured through the health centers in close collaboration with the public endocrinologists. To standardize the procedure of screening, initial management and follow-up in the intervention facilities, study algorithms that are based on both nationally and internationally recommended glycaemia thresholds for GDM testing and monitoring have been developed in consultation with the national research group on GDM and regional endocrinologists at referral level (for algorithms see Figs. 1 and 2). The health care facilities that act as controls will screen for gestational diabetes and manage affected women according to their usual practice in accordance with existing national guidelines [13].

**Fig. 1 Fig1:**
[figure not shown]
GDM screening algorithm

**Fig. 2 Fig2:**
[figure not shown]
GDM management algorithm

### Outcome variables

#### Health effects

Primary outcome is birthweight to assess whether or not there is a statistically significant difference in birth weight between the two groups after adjusting for gestational age. Secondary outcomes include weight gain during pregnancy, average glucose levels and pregnancy outcomes including mode of delivery, presence or absence of obstetric (pre/eclampsia, prolonged labor, shoulder dystocia) or newborn (hypoglycemia, respiratory distress, cardiomyopathy) complications.

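### The primary comparison is a birthweight difference adjusted for gestational age, but the test given for continuous variables cannot adjust, and no other stated analysis is named as the between-arm test

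*Protocol article*

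**What the plan says.** Four places in the protocol article bear on how birthweight is compared between arms.

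- **Outcome variables, Health effects.** The primary question is whether there is a "statistically significant difference in birth weight between the two groups after adjusting for gestational age".
- **Data analysis, general rule.** "continuous variables will be analyzed by using the Wilcoxon rank-sum test". Birthweight is continuous and is not exempted.
- **Data analysis, next sentence.** "Regression analysis will be applied to assess the relationship between the primary outcome birthweight and maternal determinants". Neither study arm nor gestational age is named as a term.
- **Population and sample size.** The trial is sized "for the assumption of a weight difference of 300 g between intervention and control group", and further: "a power of 80%, an alpha of 0.05 and an intra-class correlation coefficient of 0.1, we require 75 women with GDM in each arm".

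The section on the unit of randomization also promises an adjustment for effects between clusters at the analysis stage. It presents this as a remedy for neighbouring health centres ("As simple random selection does not account for contiguity, adjustments for" …) and gives no method.

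**The concern.** The outcome section and the analysis section give different instructions for the same variable. One requires adjustment for gestational age; the other assigns a two-sample rank test that has no place for a covariate. The sample size is built on a difference in grams, and the rank-sum test as planned does not report one.

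At stake is which result counts as the trial's answer. A rank-sum p-value and a regression p-value for birthweight can fall on opposite sides of 0.05. If neither is named primary in advance, the choice can be made after both are known. Gestational age is also commonly a strong predictor of birthweight, so an unadjusted test may give up precision.

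**Working it through.** **1. What each stated analysis can deliver**

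| Requirement | Rank-sum rule | Regression sentence |
|---|---|---|
| Compares the two arms | Yes | Not stated; arm is not named |
| Adjusts for gestational age | No; takes no covariate | Possible; gestational age is not named |
| Gives an adjusted difference in grams | No | Possible, if arm and gestational age are terms |
| Named as the primary test | No | No |

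Study arm is allocated to the health centre, so it is not naturally read as a maternal factor. Neither column, as written, satisfies the outcome definition.

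**2. What the sample size assumes**

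Inputs from the article: difference 300 g, power 80%, alpha 0.05 (two-sided assumed), ICC 0.1, at least 8 women per health centre, 10 health centres per arm. No SD is given, so 75 per arm cannot be reproduced from the article alone. With an assumed SD of 500 g:

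- Individually randomised n per arm = 2 × (1.96 + 0.84)² × 500² / 300² = 43.6, rounded up to 44.
- Design effect = 1 + (8 − 1) × 0.1 = 1.7.
- 44 × 1.7 = 74.8, rounded up to 75, as stated.

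The SD that returns 75 at cluster size 8 is about 503 g. The result is sensitive to it: 400 g gives 48 per arm, 450 g gives 62, 550 g gives 91 and 600 g gives 108. The stated figure is therefore consistent with comparing mean grams between arms with an allowance for clustering, which is not what the rank-sum rule describes.

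**3. What adjustment might be worth (illustration only)**

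Assumptions not in the article: SD 500 g, gestational-age SD 1.5 weeks, and 100–200 g of birthweight per week. Share of variance explained, R² = (slope × 1.5)² / 500²:

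- 100 g per week: 150² / 500² = 0.09
- 150 g per week: 225² / 500² = 0.20
- 200 g per week: 300² / 500² = 0.36

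For 10 clusters of 8 per arm, between-cluster variance is 0.1 × 500² = 25,000 and within-cluster variance is 225,000.

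Unadjusted SE = √[2 × (25,000 + 225,000/8) / 10] = 103.1 g. Power at 300 g from the noncentral t on 18 df is 0.786.

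Adjusted SE has two bounding cases:

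- *Proportional:* gestational age removes the same share between and within clusters, so SE = 103.1 × √(1 − R²).
- *Within only:* it removes R² × 250,000 from the within-cluster part alone, so SE = √[2 × (25,000 + (225,000 − R² × 250,000)/8) / 10].

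| R² | SE, proportional | Power | SE, within only | Power |
|---|---|---|---|---|
| 0.09 | 98.3 g | 0.82 | 100.3 g | 0.81 |
| 0.20 | 92.2 g | 0.87 | 96.8 g | 0.83 |
| 0.36 | 82.5 g | 0.93 | 91.5 g | 0.87 |

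Power thus goes from about 79% to between 81% and 93%. Both ends of this comparison are cluster-level t analyses; neither is the Wilcoxon test.

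**The case against.** The strongest reply is that the rank-sum sentence is a generic rule and that the next sentence, the only one in the analysis section to name birthweight as the primary outcome, assigns regression. Read with the outcome definition and the promised cluster adjustment, the regression could be the intended vehicle, and its list of terms is the kind of detail a condensed article leaves to an analysis plan.

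Part of this stands. A reader might infer that the plan certainly never makes its primary comparison; that is the literal reading but not the only one. The missing covariate list is not the finding. What remains is a conflict between stated rules: the test that is named has no exception for birthweight and cannot adjust, and the regression is aimed at maternal factors and not put forward as the test of the intervention. On the charitable reading there are still two birthweight analyses with no order between them.

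Three further inferences go too far.

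- *That a rank-sum test cannot yield grams at all.* A Hodges–Lehmann shift is in grams. None is planned, though, and it would not be adjusted for gestational age.
- *That the plan is underpowered without adjustment.* The unadjusted cluster-level figure of 79% is essentially the planned 80%, and nothing in the sample size section assumes adjustment. Leaving gestational age out forgoes a possible gain.
- *That the rank-sum rule inflates false positives through the missing adjustment.* In simulation under the null (5000 runs, SD 500 g, ICC 0.1, birthweight–gestational-age correlation 0.5) the rank-sum test rejected in 12.6% of trials with gestational age balanced, but that excess comes from ignoring clustering, a separate matter. Rates of 23–38% arise only if the arms are assumed to differ by 0.3–0.5 SD in gestational age. The article supports no such difference, and one caused by the intervention would be part of its total effect, not an error.

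**Conclusion.** Wrong as written. The outcome definition requires a between-arm comparison adjusted for gestational age; the analysis section assigns a test that cannot adjust, and its only regression is not designated as that comparison. This rests on the article's own statements and needs no outside figure.

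The main consequence is an undefined primary result, not a demonstrated loss of power. The 79% to 81–93% range depends on the assumed SD of 500 g, on gestational age explaining 9–36% of variance, and on whether it explains variance between health centres as well as within them. It should be cited only as an illustration.

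**What to change.** - Exempt birthweight from the Wilcoxon rule in the Data analysis section.
- State one primary analysis: regression of birthweight on study arm, gestational age at delivery and district, with health centre as the cluster, by either a mixed model or a two-stage cluster-level analysis. Choose one in advance.
- Report the adjusted difference in grams with a 95% confidence interval.
- Report the estimate without gestational age beside it. Gestational age at delivery is measured after randomisation and may respond to the intervention, so the two estimates answer slightly different questions.
- Label the regression on maternal factors as secondary or exploratory.

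The cost is analysis wording only. Table 1 already lists last menstrual period, delivery date and newborn weight among the individual data collected, and the sample size need not change.
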